### Sample Size Calculation

In the SC4C pilot study, there was a 7% reduction in GP referrals to hospital EDs and OPs, but we have powered our trial using a conservative 4% reduction [19,32]. The sample size of 18 practices with at least 60 pediatric consultations per practice per month will have 90% power to detect a 3.7% reduction (from the baseline rate of 10%) in the percentage of children who are referred to OP clinics or EDs following their GP appointment, assuming an intracluster correlation of 0.06 (derived from the pilot data [19]) and 2-sided type I error of 0.05. With the same sample size, we will have 80% power to detect a 5.5%‐6.55% reduction in the proportion of referrals to OP or ED for our planned stratification analysis by practice rurality, GP baseline referring level, years of practice, and gender.

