### Statistical Analysis

We will undertake descriptive analysis to describe the GP referral rate alongside the numbers of all children seen and the numbers of children referred to OP or ED by month during the study period for each practice.

All available data from each recruited GP and family will be analyzed according to an intention-to-treat principle. For the outcomes of GP referrals identified using the GP EMR data (eg, GP referral to OP clinic or ED), we will conduct mixed effects logistic regression, fitted to data collected during the control and intervention periods. The model will include a fixed effect of group (intervention vs control) and adjust for calendar time (as a continuous variable), and random effects to allow for variation in the outcomes for 3 hierarchical levels, including GP practice, GP within each practice, and patients seen by each GP.

Secondary outcomes collected at the child consultation level will be analyzed similarly, with separate models for the 5 common childhood conditions to measure quality of care. GP survey outcomes will be analyzed using mixed effects logistic regression, again including a fixed effect for group by intervention status and calendar time, and a random effect for GP practice, GPs, and patients.

We will control for baseline levels of GP referral for each practice in the analyses, GP-level factors (eg, rurality of the practice’s location, billing type, GP gender, years of practice, and number of children patients seen per week), and patient-level sociodemographic factors (eg, age at the encounter and socioeconomic status of residence). We will also consider whether the intervention effect varies by rurality of practice and GP-level factors (eg, referring level during baseline, years of practice, and GP gender) by the inclusion of interaction terms between group (intervention vs control) and these variables in the regression models.

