We will assess whether the correlation structure has been mis-specified. The primary analysis will assume an exchangeable within-cluster correlation structure, meaning that the correlation between any 2 individuals within the same cluster is considered constant. To evaluate the impact of potential misspecification, we will conduct a sensitivity analysis using a block-exchangeable correlation structure within periods. This structure assumes stronger correlations among individuals within the same period, with weaker correlations across different periods. To implement this, we will extend the random-effects model to include an interaction between time and the GP practice random effect.

Prior to analysis, we will understand the mechanisms of the occurrence of missing data in the primary and secondary outcomes. If there is a small number of missing data (<5%), complete case analysis will be presented as the primary analysis. Missing data can occur due to 2 main reasons, considering the current study design: the pop-up failure to launch due to technical issues (nonmonotone missingness), and GP or GP practices withdrawal from the trial (generally monotone missingness, though could also be instances of nonmonotone, for example, personal leave such as maternity leave and retirement). It is reasonable to assume that data missing due to technical failure or personal leave occur missing completely at random. Based on our knowledge, the main reason for GP and GP practice withdrawal is the GP leaving the participating practice. Therefore, it is reasonable to assume these missing data occur as missing at random, and we will undertake multiple imputation to account for the impact of the missing data on the outcomes. It is unlikely that data is “missing not at random (MNAR)” in the nature of this current study, that is, GPs withdraw from the study because of their referral patterns, and this cannot be accounted for by all observed data. If we identify any MNAR, we will not impute the data and will report and discuss the results with limitations and the reasons potentially responsible for the missingness.

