### Limitations

The stepped wedge design is susceptible to trends over calendar time, and delay in the implementation of the model could potentially decrease motivation to participate and subsequently increase withdrawal, although researchers will maintain regular contact with prospective practices through regular “touch points,” newsletters, and emails to support motivation and engagement. Results may not be generalizable due to the general practices self-selecting to participate. In a real-world setting, cooperation of GP practices in such a study is crucial to engagement, and we actively target recruitment of a diverse range of practices through PHNs and GP networks, aiming to reach GP practices that care for underrepresented or harder-to-reach population groups, for example, remote, regional, rural general practices. General practices that only use BP or MD EMR software are included for compatibility with GHRANITE, although these EMRs are used by ≈90% of general practices in Australia [27]. Extracted data that are collected from GP EMR may not represent the true scope of care provided by the GPs who also make notes in free text, which could provide a more comprehensive assessment of care quality provided. Nevertheless, the GHRANITE data extraction tool provides a robust mechanism and is the only one of which we are aware that can extract useful data from GP practices in Australia. The voice of consumers relies on voluntary agreement to respond to pre- and postintervention surveys as well as to participate in a postintervention interview. The voice of consumers is important, and we recognize the inherent risk posed by poor participation. Nevertheless, participants are aware that this is voluntary, and their data are provided anonymously. Budget constraints also have meant that family surveys are restricted to English-speaking populations, limiting the generalizability of our findings outside these groups. To highlight the consumer voice, in further implementation and scale-up of this integrated model of care, consumer engagement will need to be a focus, including prioritizing non–English-speaking and other priority population consumers. Financial constraints also limit the collection of sustainability data beyond the period post intervention, which may underestimate the ongoing need for support between GPs and pediatricians in an ongoing manner.

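### The rurality interaction model assumes one referral trend for all practices, so about half of any trend specific to rural or metropolitan practices would be read as a subgroup effect

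*Protocol article*

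**What the plan says.** The Statistical Analysis section defines the primary model as a mixed effects logistic regression "fitted to data collected during the control and intervention periods". On its fixed effects it says: "The model will include a fixed effect of group (intervention vs control) and adjust for calendar time (as a continuous variable"). Random effects are for practice, GP and patient.

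On effect modification it says: "We will also consider whether the intervention effect varies by rurality of practice and GP-level factors", naming baseline referring level, years of practice and GP gender. The method is "by the inclusion of interaction terms between group (intervention vs control) and these variables in the regression models". No term lets the calendar trend differ by moderator.

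Three other places bear on this:
- The Sample Size Calculation section gives 80% power for reductions of 5.5 to 6.55 points "for our planned stratification analysis by practice rurality, GP baseline referring level, years of practice, and gender".
- A sensitivity analysis on the correlation structure says: "we will extend the random-effects model to include an interaction between time and the GP practice random effect".
- The Limitations section concedes: "The stepped wedge design is susceptible to trends over calendar time".

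**The concern.** In a stepped wedge trial, intervention status and calendar time move together, and the time term keeps a background trend out of the intervention effect. The plan gives the overall effect that protection. The subgroup terms get it only if all strata follow the same trend, because there is a single slope for everyone. If referral rates drift differently in rural and metropolitan practices for reasons unrelated to the intervention, the group-by-rurality term absorbs part of the difference.

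At stake is the reading of whether the virtual model works differently outside metropolitan areas. If rural referral rates were rising faster for outside reasons, the intervention would look less effective in rural practices and more effective in metropolitan ones. If they were rising more slowly, the reverse would hold.

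**Working it through.** **Layout (Trial Design, Sample Size Calculation and Results sections).** Data run from September 2023 to February 2025, which is 18 months. There are 18 practices; three switch each month from month 2, giving 6 steps. A practice in step s has s control months, one excluded embedding month and 11 analysed intervention months. Control data therefore lie in months 1 to 6 only. Within a practice, the mean intervention month is 7.0 months (step 1) to 9.5 months (step 6) later than the mean control month.

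**Variance inputs.** 60 consultations per practice-month, ICC 0.06, baseline 10%:
- total variance 0.10 × 0.90 = 0.09
- between practices 0.06 × 0.09 = 0.0054
- cell mean within practice 0.09 × 0.94 / 60 = 0.00141

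The calculation is generalised least squares (GLS) on the risk scale with a practice random effect. GP and patient levels are collapsed into the practice.

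**The plan's own figure first.** The stated power is 90% for 10% to 6.3%.
- A standard 7-period, 6-step layout with categorical time gives SE 1.17 points and power Φ(3.7/1.17 − 1.96) = 88%.
- The 18-month layout with categorical time gives 85.6% using the variance at 10%, and 91.2% using the variance at the mean of the two rates.

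The set-up is close enough to the plan's to be used.

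**Bias of the interaction.** Assumptions not in the documents: 9 rural and 9 metropolitan practices placed at random across steps, no true interaction, and a rural slope 0.1 point per month above the metropolitan slope.
- Model with group, time, rural and group × rural: false interaction 0.855 points, split as about +0.43 in rural and −0.43 in metropolitan practices.
- The differential drift over the study is about 0.1 × 18 = 1.8 points, so 0.855/1.8, or about half, lands on the interaction.
- Adding time × rural: false interaction 0.00.

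The bias is the same to within 0.001 point with 6 or 12 rural practices.

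**False-positive rate.** With bias b and standard error SE, the rate is 1 − Φ(1.96 − b/SE) + Φ(−1.96 − b/SE). SE is 1.12 points in the shared-time model.

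| Assumed slope difference (points/month) | Bias (points) | False-positive rate |
|---|---|---|
| 0 | 0 | 5% |
| 0.05 | 0.43 | 6.7% |
| 0.1 | 0.86 | 11.9% |
| 0.2 | 1.71 | 33.4% |

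For example, at 0.1 the ratio b/SE is 0.855/1.12 = 0.76, which gives about 12%. With 6 or 12 rural practices the rates at 0.05, 0.1 and 0.2 are about 6.5%, 11% and 30%.

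**Check on the logistic scale.** A separate simulation used 1000 trials per scenario, a practice SD of 0.8 on the logit scale, and 10% to 6.3% in both strata. One stratum's underlying rate drifted over 18 months:
- no drift: 4.9%
- drift to 11%: 7.5%
- drift to 12%: 12.2%
- drift to 12% with the time × rural term: 4.9%

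At 12%, the interaction took up 0.105 of the 0.205 log-odds drift, again about half.

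**Does the planned sensitivity analysis help?** Under a block-exchangeable structure with an assumed cluster autocorrelation of 0.8, the bias is 0.854 points, so it is unchanged. If the practice-by-time term is read instead as a random practice slope (assumed SD 0.1 to 0.2 points per month), the bias falls only to between 0.79 and 0.63 points.

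**Price of the extra term.** SE rises from 1.12 to 1.79 points, a ratio of 1.6. The interaction detectable with 80% power is 2.80 × SE, so it goes from 3.1 to 5.0 points. The variance ratio (1.12/1.79)² = 0.39 means that about 61% of the shared-time model's information comes from assuming equal trends.

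**The case against.** The strongest case against is that this is a condensed article. One sentence says the team will consider effect variation; it writes out no full model and does not rule out stratum-specific time, which an analysis plan could supply. The Sample Size Calculation section also speaks of stratification, and its figures look like separate-stratum fits. Scaling the overall 3.7 points at 90% power to one third of the practices gives 3.7 × (2.80/3.24) × √3 = 5.5 points, the lower stated figure. Separate fits would each carry their own time term.

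Part of this stands. The match is an inference, since that section names neither method nor split, but it does suggest that two different analyses are described. It does not remove the point: where the article states a method, it adds group-by-moderator terms to a model with one time term, and following that rule builds in equal trends.

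Other parts of the objection stand in full, and they limit what a reader may infer:
- **That a differing trend exists.** The documents report none. At 0.05 points per month the harm is small.
- **That all of such a trend would become a subgroup effect.** About half would.
- **That the confidence interval is too narrow.** Without drift the test keeps its 5% level. With drift the fault is bias, not an understated variance.
- **That rurality is a listed objective.** Nonmetropolitan access motivates the trial, but neither the Objectives section nor Table 1 lists a rural-versus-metropolitan comparison.
- **That all four moderators are equally exposed.** The plausible mechanisms are geographical. GPs of different gender or experience may share a practice and local services, and no case for differing trends has been made for those factors.

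**Conclusion.** The point holds in limited form. As stated, the effect-modification model assumes equal referral trends across strata. With all control data in the first third of the study, about half of any stratum-specific trend would appear as a subgroup effect of the intervention. The sizes (about 7%, 12% and 33% false positives) rest on assumed slope differences, an assumed 9/9 split and a linear risk-scale approximation; the logistic simulation gives similar results.

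The model's own calendar-time term and the randomised start times protect the overall effect, and nothing here suggests that it is biased. This is a weakness of a secondary analysis that should be corrected before any rurality difference is interpreted.

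**What to change.** In the Statistical Analysis section:
1. For rurality first, add a moderator-by-calendar-time term beside the group-by-moderator term, in the same form of time as the main model. Alternatively, fit separate models by stratum, each with its own time term. Do the same for the other moderators where a differing trend is plausible.
2. Report this together with the shared-time model. Claim a subgroup difference only if it does not depend on the equal-trend assumption.
3. Reconcile the stratification wording in the Sample Size Calculation section with the interaction wording in Statistical Analysis, so that one analysis is described in both places.

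No new data are needed. The cost is the precision shown above: a detectable interaction of about 5.0 points exceeds the 3.7-point overall target, so a null interaction will say little. The precision given up comes from the equal-trend assumption. No stated power is lost, because the Sample Size Calculation section gives no detectable interaction, only reductions of 5.5 to 6.55 points for the stratified analysis.

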### Economic Evaluation

From a health sector perspective, a within-trial economic evaluation will be conducted following methodological and reporting guidelines [33-35]. The investment costs of conducting SUSTAIN (including GP training, practice administrative support, pediatrician time, consults, and case-study discussions) will be assessed relative to GP usual care using standard price lists and any patient out-of-pocket payments (including Medicare Benefits Schedule, Pharmaceutical Benefits Schedule, and Independent Hospital Pricing Authority). The costs (and cost offsets) associated with changes in study outcomes (including ED presentations and OP attendances) will then be estimated using similar methods and aligned with the statistical analysis (described above). Three forms of complementary economic analysis and metrics will then be conducted using the information generated. First, the incremental net cost per referral avoided (primary study outcome) will be generated relative to usual care to estimate cost-effectiveness. Second, a return on investment will assess (expected) net cost offsets from avoiding ED/OP relative to the investment in SUSTAIN, and changes in Medicare Benefits Schedule/Pharmaceutical Benefits Scheme use. Probabilistic sensitivity analysis will assess statistical uncertainty in both analyses and the cost-effectiveness acceptability curves generated. Third, a budget impact analysis [36] will estimate the costs of implementing the model at the national level and disaggregated by multiple potential payers (State and Commonwealth). This will inform affordability considerations and combine with wider trial findings to guide translation and sustainable implementation.

### Implementation Evaluation

#### Overview

The mixed methods implementation evaluation for SUSTAIN will be based on the methodology developed for the SC4C trial [37]. We will use the Consolidated Framework for Implementation Research (CFIR) [38] to understand the effectiveness of the SUSTAIN model in driving systems change, while also identifying contextually relevant strategies for successful implementation. Factors (ie, barriers and facilitators) identified as moderating the adoption, delivery, and maintenance will also be used to inform wider state and potentially national rollout. The mixed methods evaluation will allow us to assess implementation metrics as defined by Proctor et al [39] (Table 3).

**Table 3. T3:** Trial implementation metrics.

	Questions addressed by each implementation factor
Acceptability	Do practitioners, parents, and children view the SUSTAIN model as agreeable?
Adoption	To what extent do practitioners and parents use the SUSTAIN model?
Appropriateness	Do stakeholders perceive SUSTAIN as relevant and useful?
Fidelity	Is SUSTAIN applied as intended? Are all component parts of the intervention delivered as planned?
Coverage	How many service users of those eligible are reached?
Cost	How much does it cost to successfully implement SUSTAIN?
Sustainability	What are the factors that will allow SUSTAIN to be scaled up further?

A logic model (Figure 3) has been developed to inform the implementation evaluation guided by the implementation research logic model [40]. The logic model encompasses the specific contextual determinants that the implementation evaluation would need to consider, both within (eg, inner context representing individual factors and organizational settings) and external to the sites (eg, area demographics and socioeconomic status). In addition to the contextual factors, the logic represents the measurable intervention characteristics, implementation strategies, mechanisms of action, and outcomes.

**Figure 3. F3:**
[figure not shown]
Trial logic model. GP: general practitioner; PHN: primary health network; SCHP: Sydney Child Health Program.

The implementation evaluation will use a mixed methods approach; findings will be triangulated as in our previous studies [41,42].

Surveys with GPs will be conducted at the start of and end of the intervention. GPs survey will include 2 validated instruments: the short intervention acceptability, appropriateness, and feasibility measure, and the NoMAD tool, based on the Normalization Process Theory, which assesses to what extent practitioners “buy into” SUSTAIN [43-45]. The survey will assess their experience of the current model of care and confidence in pediatric care. All GP instruments have been used in our previous SC4C trial and shown to be acceptable and feasible to use.

To determine individuals' knowledge and beliefs about the model of care, relative advantages of the model of care, GP and pediatrician self-efficacy, barriers and facilitators affecting the delivery of the intervention both from an individual and organizational perspective, the appropriateness and acceptability of the intervention; and recommendations for future implementation, we will conduct focus groups or interviews with GPs, practice managers, administrative staff, pediatricians, and families who participated in coconsultations. Interview guides have been derived from the CFIR. Practice managers and administrative staff will specifically be asked about how the model of care affected the normal operation of general practices. GPs and pediatricians will specifically be asked about features of the working relationship, for example, the collaborative nature of the relationship. Interviews with family members will determine their perceptions of the acceptability of the SC4C model and any potential adaptations to the model to make it more acceptable for families of children presenting to GP practices. Additionally, feedback from general practice staff and pediatricians will be routinely collected (eg, through meetings and email) to provide ongoing support during the implementation.

As described above, GPs will be asked to complete a short web-based survey before and after the intervention rollout via REDCap. As part of the implementation evaluation, GPs, practice managers, and administrative staff in participating practices will be contacted to participate in a focus group within each practice, with the option for an individual interview ≈6 months into the intervention and individual interviews with GPs at the end of the intervention at 12 months. Feedback will be used to determine appropriateness and acceptability of the intervention, identify barriers and enablers affecting delivery of the intervention, and sustainability of the model. The focus groups and interviews will be facilitated by investigators responsible for the implementation evaluation, and prior to the focus group or interview, the researcher will describe to participants the reasons for conducting the interview or focus group and provide a participant information sheet and a web-based consent form. The researcher will respond to any participant questions or concerns and inform participants that they can stop the interview at any time and revoke their consent to participate during or after the interview. In this event, interview recordings and transcripts will be removed from the trial and destroyed.

Family surveys conducted during the intervention period will include an item seeking permission to contact them about the opportunity to participate in a voluntary qualitative interview via telephone or web. This opportunity will only be open to families who have participated in a GP-pediatrician coconsultation, which will be determined earlier in the survey. When contacting parents or caregivers, the researcher will describe the reasons for conducting a follow-up interview, will not ask for the identity of their GP, and reassure parents that any information obtained will be confidential and will have no impact on the care their child receives from their GP. They will be asked to sign a web-based consent form.

The researcher will respond to any parent’s or caregiver’s questions or concerns and inform participants that they are able to stop the interview at any time and revoke their consent to participate during or after the interview. In this event, interview recordings and transcripts will be removed from the trial and destroyed.

Implementation evaluation data collection and analysis will assess the following.

